#### Process measures

To evaluate the uptake of the intervention and the adherence to the consensus-based IRIS study protocol for the detection and management of IUGR, a number of process measures will be assessed, including the rate of women declining participation, the proportion of protocol violations, proportion of disagreements in primary outcomes based on reassessments by research assistants/nurses, and opinions of midwives on (in)effective elements of the intervention. Data on protocol adherence will be collected via standardized forms filled out by a researcher attending several multidisciplinary case evaluations or audits in case of perinatal deaths or severe adverse perinatal outcome. Protocol adherence will also be assessed via standardized case report forms filled out by research assistants/nurses using hospital records of a subsample of neonates and women (n ~ 2000) displaying perinatal/postpartum morbidity/mortality (for more detail see subsection data collection). Using a short questionnaire, we will evaluate community midwives’ experience of cooperation with healthcare professionals in secondary care in terms of the IRIS study protocol after the completion of the inclusion period.

### Data collection

#### Baseline questionnaire midwifery practice and women

Via a short questionnaire midwives will report characteristics of their midwifery practices based on the most recent Dutch national midwifery care report [46]. After enrolment, using short questionnaires, participating women and midwives will report maternal baseline characteristics, including data on demographics and anthropometrics.

#### Existing medical databases/registries

For the main study (*n* = 15,000), data will be extracted from the following existing databases: 1) the database of the Perinatal Registry of the Netherlands (Perined); 2) ultrasound centers’ databases; 3) hospital medical records of mothers and neonates if applicable. These databases will be used to collect data on (primary) clinical outcomes, obstetric variables, ultrasound scans, and care processes.

#### Survey

Two subsamples will be derived from the complete study population (see Fig. 1) for a detailed assessment of societal costs, maternal quality of life, maternal experience of healthcare during the perinatal period, maternal psychological functioning (maternal depressive symptoms, anxiety, and bonding), and infant neurodevelopment. These two subsamples comprise the following: (a) a random sample of 900 women (450 intervention and 450 CAU) who will be asked to complete online questionnaires around 22 weeks of gestation, at 32 weeks of gestation, and at 6 weeks, 6 months, and 24 months after estimated date of delivery (*n* = 15 per midwifery practice); and (b) a non-random sample comprising 600 women in whom IUGR is suspected by fetal ultrasonography (300 intervention and 300 CAU) and who will be asked to complete online questionnaires (*n* = 10 per midwifery practice) after the suspicion of IUGR during late pregnancy, at 6 weeks and 6 and 24 months postpartum. At the age of 24 months, we will ask mothers participating in the survey and mothers of toddlers having (a) severe adverse perinatal outcome(s) (see above for the definition of our primary clinical outcome) to report toddlers’ developmental milestones and behavioral problems.

For the survey, we will recruit 1500 women prenatally. Based on an expected non-response and drop-out rate of 33 %, we expect to collect complete follow-up data in 1000 women in the random (*n* = 600) and non-random sample (*n* = 400).

Women who will participate in the survey will give additional consent to participate in the survey and will receive an e-mail with a link to an online questionnaire at each measurement time point. Non-responding pregnant women will receive reminders via e-mail. To enhance participation of non-Dutch speaking women, the questionnaires will be translated into English. These questionnaire data will be collected through telephone interviews conducted by a researcher.

#### Hospital medical records

Using standardized case report forms research assistants/nurses will collect detailed information from approximately 2000 hospital medical records on healthcare utilization by and clinical outcomes of: 1) neonates who were referred to a pediatrician for neonatal admission, had a birth weight <5th percentile or a severe adverse perinatal outcome, e.g. Apgar score 5 min after birth <4, as indicated in the Perined database; and 2) women participating in the survey and being referred to a gynecologist/secondary care during the perinatal period, and women having a neonate who has been referred to a pediatrician, has a birth weight <5th percentile or a severe adverse perinatal outcome. The standardized case report forms will also be used to collect information on professionals’ adherence to the multidisciplinary consensus-based IRIS study protocol for the detection and clinical management of IUGR. By focusing on this group of neonates and women, we are able to efficiently collect data on severe adverse perinatal outcome, maternal perinatal morbidity, healthcare utilization, and protocol adherence which would not have been feasible in all 15,000 women.

### Statistical analyses

#### Sample size of the trial

Our sample size calculation was based on our primary dichotomous outcome, i.e. severe adverse perinatal outcome. Perined data suggest that the expected rate of severe adverse perinatal outcome in the source population, i.e. low-risk pregnant women in the Netherlands, is 1.54 %. Neither nationally nor internationally it has been agreed which degree of reduction in severe adverse perinatal outcome can be considered as feasible and clinically relevant. Therefore, the IRIS study group decided to aim at a reduction from 1.54 % to 1.0 % in the primary outcome. With 80 % power and a significance level of *p* < 0.05, 13,536 pregnant women should be included. Yet, due to the clustered design our sample size calculation also needs to take dependency of data into account. Pagel et al. (2011) estimated the intracluster correlation coefficients (ICCs) for a range of offspring perinatal outcomes using data from five community‐based cluster-randomized trials in three low‐income countries [47]. Five ICCs ranging from 0.0003 to 0.002 were reported for neonatal mortality [47]. We expect the ICC in the IRIS study to be much more similar to 0.0003 than to 0.002 for the following two reasons. First, the ICCs presented in the paper by Pagel et al. (2011) are based on prevalence rates of neonatal mortality ranging from 1.5 % to 5.9 % indicating a higher maximum rate than the rate of severe adverse perinatal outcome expected for the IRIS study, i.e. 1.54 % [47]. Since ICCs are expected to be related to low prevalences of the outcome of interest, we may assume the ICC in the IRIS study to be even lower than 0.0003. Second, participating midwifery practices will offer both CAU, and later on, routine third trimester ultrasound screening. Due to this, the variation in characteristics and practice management between the clusters, i.e. midwifery practices, will be reduced and, consequently, the size of the ICC will be lowered. Using the formula to correct for clustering [1 + (n‐1) * ICC] with *n* = 250, i.e. average cluster size in our study, the required sample size for the IRIS study is 14,547 women. Since not all pregnant women may be recruited exactly at 20–22 weeks of pregnancy, we decided to include a total of 15,000 pregnant women.

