## Discussion

Sensitive measures to detect IUGR during late pregnancy and subsequent adequate clinical management of IUGR are important to decrease perinatal mortality and morbidity. This large-scale nationwide stepped wedge cluster-randomized trial will provide evidence whether or not routine third trimester ultrasound screening in combination with protocolized management is clinically effective and cost-effective as compared to CAU in reducing severe adverse perinatal outcome.

The current study has several strengths: it will fill crucial knowledge gaps in the domain of screening for and management of IUGR and is, therefore, expected to have important clinical implications. First, a major spin-off of the IRIS study is the development of a consensus-based multidisciplinary protocol for the detection and management of IUGR. This protocol can be used as starting point for the development of a multidisciplinary guideline for prenatal care of IUGR in the Netherlands. Second, as recommended in the recent Cochrane review by Bricker et al. (2015), the current study extends previous work by investigating the impact of routine third trimester ultrasound screening on maternal prenatal and postnatal psychological functioning and on long-term offspring neurodevelopmental outcome [14]. Third, we will identify pregnant women’s and professionals’ ethical dilemmas related to positive, unexpected and unclear findings during ultrasound screening. Based on these results recommendations for future practice can be formulated. Fourth, a methodological strength of our trial is its large sample size. In comparison to most previous studies [14], the current trial is adequately powered to examine whether third trimester ultrasound screening can reduce severe adverse perinatal outcome. Finally and importantly, our trial examines the cost-effectiveness and cost-utility of routine third trimester ultrasound screening among low-risk pregnancies as compared to CAU.

The results of the effectiveness and cost-effectiveness study will assist healthcare providers and policymakers in making an educated choice about whether or not introducing routine third trimester ultrasound screening in the Netherlands.

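### The sample size uses a parallel-cluster design effect; with calendar period in the model, this stepped wedge has about 49% power, not 80%

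*Protocol article*

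**What the plan says.** The section on the sample size of the trial sets out to "aim at a reduction from 1.54 % to 1.0 % in the primary outcome". It then gives the unadjusted total: "With 80 % power and a significance level of *p* < 0.05, 13,536 pregnant women should be included".

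For clustering it draws on a published set of values: "Five ICCs ranging from 0.0003 to 0.002 were reported for neonatal mortality". It adds: "We expect the ICC in the IRIS study to be much more similar to 0.0003 than to 0.002", and argues that the true value may be below 0.0003. The correction is described as follows: "Using the formula to correct for clustering [1 + (n‐1) * ICC] with *n* = 250, i.e. average cluster size in our study". The result is "the required sample size for the IRIS study is 14,547 women", after which "we decided to include a total of 15,000 pregnant women".

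The sections on study design and on recruitment and randomization, with the legend of Fig. 2, describe a stepped wedge. All 60 practices start in control, a third change over at three-month intervals, and women are enrolled over months 1 to 12. The abstract gives 7,500 women per condition. The effectiveness analysis is a multilevel logistic regression adjusted for practice and for medical, demographic and life-style confounders. It names no calendar period or step.

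The Discussion states that "the current trial is adequately powered to examine whether third trimester ultrasound screening can reduce severe adverse perinatal outcome".

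**The concern.** The factor 1 + (n − 1) × ICC belongs to a parallel cluster trial, in which both conditions run side by side throughout. In this design the first quarter is all control and the last is all intervention, so only months 4 to 9 contain both. Randomization protects the comparison only within calendar time, and the information lost by comparing within periods appears nowhere in the calculation.

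The Background criticizes most earlier trials as underpowered, and the Discussion presents this one as the remedy and as a basis for policy. If a time-adjusted analysis has about even odds of detecting the target effect, a non-significant result could be misread as evidence that routine screening does not work.

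**Working it through.** **Inputs from the protocol article.** Rates 1.54% and 1.0%; power 80%; significance level 0.05 (two-sided reproduces the stated figure); 13,536; ICC range 0.0003 to 0.002; cluster size 250; total 15,000; 60 practices; a third switching every three months; 12 months of enrolment; 7,500 per condition.

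**Assumptions.** The last third switches at month 9. Randomization is stated only for months 3 and 6 and Fig. 2 is not shown, but this layout gives the stated 7,500 per condition. Practices are of equal size and recruit evenly, so each contributes 15,000 / (60 × 4) = 62.5 women per quarter. Women are classed by their practice's status at enrolment.

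**1. The plan's own figures.** The two-proportion formula (two-sided 0.05, 80% power, no continuity correction) gives 13,498 in total, within 0.3% of 13,536. The design effect is 1 + 249 × 0.0003 = 1.0747, and 13,536 × 1.0747 = 14,547. Both figures reproduce, and the ICC used is therefore 0.0003.

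**2. Cost of period adjustment at ICC 0.** The proportion of practices on intervention in the four quarters is 0, 1/3, 2/3 and 1.
- The variance of the treatment indicator within quarters is 0, 2/9, 2/9 and 0, averaging 0.111. Over the whole sample it is 0.25.
- Variance inflation from period adjustment is 0.25 / 0.111 = 2.25.
- With mean rate 1.27%, the outcome variance is 0.0127 × 0.9873 = 0.01254. The standard error is √(0.01254 / (15,000 × 0.111)) = 0.00274.
- Power = Φ(0.0054 / 0.00274 − 1.96) = 50%.

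**3. Full stepped wedge calculation.** Hussey-Hughes variance, 15,000 women, 1.54% versus 1.0%:

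| ICC | SE with period | Power with period | Power without period |
|---|---|---|---|
| 0 | 0.00274 | 50.4% | 84.0% |
| 0.0003 | 0.00278 | 49.3% | 83.6% |
| 0.001 | 0.00285 | 47.4% | 82.8% |
| 0.002 | 0.00293 | 45.4% | 81.9% |

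A logistic information calculation at ICC 0 gives 49.9% with period terms and 83.4% without. A simulation of 1,000 trials gives 50.5% and 83.7%.

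**4. Detectable reduction at 80% power.** Starting from 1.54% and letting the mean rate fall with the size of the effect, the detectable reduction is 0.75 points at ICC 0.0003 and 0.78 at ICC 0.002.

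**5. Sensitivity to layout and variance (ICC 0.0003, with period).** Three periods only: 61%. Last third never crossing over within 12 months: 66%. Variance taken at 1.54% or at 1.0% instead of the mean: 42% or 59%. All are below 80%.

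**6. What omitting period would mean.** The mean enrolment quarter is 3.33 for intervention women and 1.67 for control women, a gap of 1.67 quarters or 5 months. If the event rate drifted by 0.1 points per quarter (an illustrative assumption), the crude difference would move by about 0.17 points, roughly a third of the 0.54-point target.

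**The case against.** The strongest reply is that 49% is not the power of the analysis as written. The effectiveness section names no period term, and without one the same women give 82 to 84%, so the stated 80% is met. This stands as a condition on the figure: a reader might infer that the plan's power is simply 49%, and the document does not support that. It does not rescue the calculation, because the model that keeps the power lets calendar time into the effect estimate. A period term may also be specified in an analysis plan that is not shown; if so, the mismatch with the sample size is certain, not conditional.

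A reader might also blame the loss on choosing the lowest ICC. That does not hold: 49% is obtained at that same ICC, ICC 0 still gives only 50%, and moving to 0.002 costs about 4 points. Under the plan's own formula, ICC 0.002 would require 13,536 × 1.498 = 20,277 women, but that describes a parallel trial that will not be run.

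On the ICC argument itself, a rate of 1.54% at the bottom edge of the quoted 1.5% to 5.9% may favour a value near 0.0003, if ICC rises with prevalence. It lies inside that range, however, so it gives no ground for going below 0.0003. Nor does offering both conditions in every practice remove between-practice variation in outcome.

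Finally, the month 9 switch is an inference, so 49% should not be read as exact.

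**Conclusion.** The concern holds in conditional form. The sample size method does not match the stepped wedge design, although nothing is miscalculated. For a comparison adjusted for calendar period, 15,000 women give about 45 to 50% power over ICC 0 to 0.002 under the layout above, and up to about 66% at ICC 0.0003 under the other layouts examined. For an unadjusted comparison the power is adequate, but the estimate is confounded with time. So no model considered here gives both protection against secular trend and 80% power for the planned 0.54-point reduction, and the Discussion's claim of adequate power is not supported. For scale only, 80% power with period adjustment would take about 32,000 women at ICC 0.0003, with 60 practices. The ICC choice is a secondary matter.

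The figures rest on equal practice sizes, even recruitment, classification by status at enrolment and variance at the mean rate. Letting within-practice correlation decay between periods (cluster autocorrelation 0.8) leaves the result at 49%.

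**What to change.** 1. In the effectiveness analyses, name calendar period (step) as a fixed effect in the primary model.
2. In the sample size section, replace the parallel design effect with a stepped wedge calculation that includes period effects, over ICC 0.0003 to 0.002. State when the last third switches.
3. Restate the power at 15,000 women as about 45 to 50% for 1.54% versus 1.0% under that layout, and give the reduction detectable with 80% power as about 0.75 to 0.78 points.
4. Drop the suggestion that the ICC may be below 0.0003.
5. Remove the adequate-power claim from the Discussion, and say that a non-significant result will be interpreted from its confidence interval.

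The cost is rewording in three places and a less favourable stated power. No additional women or practices are requested.

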## Methods/design

### Study design

The IRIS study is a nationwide stepped wedge cluster-randomized trial among 15,000 low-risk pregnant women receiving care at 60 midwifery practices in the Netherlands. The intervention entails routine third trimester ultrasound screening combined with serial fundal height measurements and clinically indicated ultrasonography, while the control condition entails CAU (serial fundal height measurements and clinically indicated ultrasonography only). In 1500 pregnant women derived from the entire study population a survey will be conducted to assess societal costs, maternal psychological functioning, maternal quality of life, and infant neurodevelopment. The exact design of the survey will be described in more detail later on.

Two sub-studies will be conducted as part of the IRIS study. In sub-study A, a Delphi study will be conducted to develop a multidisciplinary consensus-based protocol for the detection and subsequent management of IUGR in the Netherlands. Sub-study B will address ethical considerations of additional/routine third trimester ultrasound screening. These sub-studies will be described in more detail later on.

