**Fig. 1 Fig1:**
[figure not shown]
Flow chart study design

During the first consultation after the 20-weeks pregnancy ultrasound screening has been offered, eligible pregnant women will be given a trial information leaflet by their midwife. The midwife will obtain consent.

Midwifery practices will form the unit of randomization. Randomization per practice rather than per midwife or woman minimizes contamination and maximizes contrast between the intervention and control group. As shown in Fig. 2, all midwifery practices (*n* = 60) will start in the control group. At 3 months intervals, a third of the midwifery practices will change status from the control to the intervention condition. To balance the number of women in the two conditions, practices will be stratified before randomization in large and small practices, with the average practice size as cut‐off (250 women per year). A stratified computer‐generated random sequence will determine the order in which practices change from control to intervention status. Randomization will be conducted by an independent statistician at 3 and 6 months after the start of baseline data collection and the recruitment of the first participating women.

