**Fig. 2 Fig2:**
[figure not shown]
The stepped wedge design of the IRIS study. Pregnant women will be enrolled during months 1–12 at 20–22 weeks of gestation. All midwifery practices (*n* = 60) will start with the control condition providing care as usual. At intervals of 3 months, a third of all practices will change status from the control to the intervention condition, which means providing routine third trimester ultrasound screening at 28–30 weeks and 34–36 weeks of gestation. Postnatal follow-up will be conducted in months 18–42

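### The target of 15,000 equals the full stated annual volume of the 60 practices, so 80% power holds only if about 97% of that volume is eligible and consents

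*Protocol article*

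**What the plan says.** All references are to the protocol article.

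- **Study design** describes "15,000 low-risk pregnant women receiving care at 60 midwifery practices in the Netherlands".
- **Recruitment and randomization** stratifies practices as large or small. The cut-off is the average practice size, given as "250 women per year".
- **The legend to Fig. 2** fixes the window: "Pregnant women will be enrolled during months 1–12".
- **Sample size of the trial** starts from 13,536 women (1.54% against 1.0%, 80% power, significance level 0.05). It applies a design effect with n = 250, described as the "average cluster size in our study", and obtains 14,547. It then says "we decided to include a total of 15,000 pregnant women". The reason given for the increase is that some women may not be recruited exactly at 20–22 weeks.
- **The eligibility section** requires a singleton pregnancy, absence of important obstetric or medical risk, reliable dating, and care in the practice at 22 weeks. Consent is obtained by the midwife.
- **Process measures** include "the rate of women declining participation".
- **Survey** allows 33% for non-response and drop-out among the 1,500 survey women.
- **The Discussion** presents the trial as having enough power, in contrast to most earlier studies.

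**The concern.** The number 250 does two jobs. It is the yearly size of an average practice, and it is the number of trial women in an average cluster. With a one-year window the two agree only if practically every woman counted in the practice size is enrolled. Yet the plan sets entry criteria, asks for individual consent and intends to measure refusals. The survey component has an explicit loss allowance, but the main trial has none for ineligibility or refusal.

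At stake is the 80% power claim. If uptake is materially below 97%, the trial has less power than stated for a rare primary outcome, and a null result could be read as stronger evidence against routine screening than it is. The article itself criticises most earlier trials as underpowered, so its own power statement will be relied on.

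**Working it through.** **Inputs from the article.** 60 practices; 250 women per practice per year; 12 months of enrolment; event rates 0.0154 and 0.010; power 0.80; significance level 0.05; equal allocation (7,500 each). The ICC is taken as 0.0003, the value that reproduces the stated total. Sidedness is not stated; two-sided reproduces the stated figure and one-sided (10,632) does not.

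**Step 1: reproduce the plan's figures.**
- Two-proportion formula with pooled variance, mean rate 0.0127: 6,749 per arm, 13,498 in total. The article states 13,536, a difference of under 0.3%.
- Design effect: 1 + (250 − 1) × 0.0003 = 1.0747.
- 13,536 × 1.0747 = 14,547, as stated.

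The sample size arithmetic is sound.

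**Step 2: stated volume against target.**
- 60 × 250 × 1 year = 15,000, which is 100% of the target.
- 14,547 / 15,000 = 0.970.
- 15,000 − 14,547 = 453 women, or 3.0% of 15,000.

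Lower uptake also shrinks the clusters and hence the design effect. Break-even is the uptake f that solves 15,000f = 13,536 × [1 + (250f − 1) × 0.0003]. This gives f = 13,531.9 / 13,984.8 = 0.968, so the threshold hardly moves.

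**Step 3: power by uptake.** Uptake f is the share of the 250 that is eligible and consents. The article gives no value, so the rows below 100% are assumptions.

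N = 15,000f; cluster size m = 250f; design effect DE = 1 + (m − 1) × 0.0003; effective N = N / DE; n = effective N / 2 per arm.

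Power = Φ{[0.0054√n − 1.96√(2 × 0.0127 × 0.9873)] / √(0.0154 × 0.9846 + 0.010 × 0.990)}.

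| Uptake f | N | m | DE | Effective N | Power |
|---|---|---|---|---|---|
| 100% | 15,000 | 250 | 1.0747 | 13,957 | 81% |
| 97% | 14,550 | 242.5 | 1.0724 | 13,567 | 80% |
| 90% | 13,500 | 225 | 1.0672 | 12,650 | 77% |
| 80% | 12,000 | 200 | 1.0597 | 11,324 | 73% |
| 70% | 10,500 | 175 | 1.0522 | 9,979 | 67% |

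**The case against.** The strongest reply is that no stated figure is wrong and that the article never says 250 is the gross caseload of the 60 participating practices. It appears once as a stratification cut-off and once as a count of trial women, and 15,000 / 60 is also 250. The number of clients per year is a baseline item still to be collected, so the recruited practices could be larger than average. These are primary care practices and the source population is described as low-risk, so much of the eligibility screening may already be reflected in the 250. Recruitment feasibility is also often left to the full protocol, which is not shown.

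Part of this stands. The 250 is ambiguous, and the loss from ineligibility may be small or nil. But if it counts eligible women, about 97% of them must still consent. If the recruited practices are larger, the article does not say so, and it gives 250 as the average in this study. Nor is the point a bare omission: the article publishes the whole chain from 13,536 to 15,000, including a reason for the last increment, and that reason is not refusal or ineligibility.

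A reader might go further and infer that the design cannot deliver 15,000, or that any deficit could not be made up. The documents support neither. Without an uptake figure the shortfall is unknown, and although the step intervals and the enrolment window are stated, nothing rules out recruiting more practices or lengthening enrolment. Power that allows for the stepped wedge structure is a separate matter and is not used here.

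**Conclusion.** The point holds as a conditional one. On the article's own figures, the target leaves no room for ineligibility, and the stated requirement leaves 3% for all losses together, a margin already assigned to another cause. The 97% threshold follows from stated numbers, provided the 60 practices average 250 women a year. The loss of power does not: it depends on an assumed uptake. Relative to 81% at full enrolment, it is about 4 percentage points at 90%, 9 at 80% and 14 at 70% (from the unrounded powers 0.813, 0.774, 0.728 and 0.673). These figures also take over the plan's ICC and its parallel-cluster formula. The unconditional claims of 80% power and of adequate power should not stand without the uptake they presuppose.

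**What to change.** In the sample size section:

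1. State whether 250 is annual caseload, eligible women in care at 22 weeks, or enrolled women.
2. Restate expected enrolment as 60 × 250 × eligible share × consenting share, omitting the eligible share if 250 already counts eligible women.
3. Use the resulting cluster size in the design effect.
4. Tabulate N and power over 70–100% uptake, and make the 80% power statement and the corresponding claim in the Discussion conditional on the uptake assumed.

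This costs a few restated sentences and one small table, with no added participants. It corrects the claim but does not restore power. If the restated power is judged too low, recovering 15,000 is a separate design decision with a real cost. At an assumed 80% uptake, for example, it would take 75 practices (60 / 0.8) or 15 months of enrolment (12 / 0.8).
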